### Participant selection

Recruitment of study participants will be performed using announcements on social media (Facebook, Instagram) and by local press and radio. The time planned for the recruiting is expected not to exceed six months. Previous experiences with human studies [44] showed that the motivation of the study participant to take part is crucial to successful trial completion. Therefore, the participants are offered the free, planned weight-loss program, which does not require cooking the meals for eight weeks, with meals balanced by a dietician and delivered to the house daily, at a time convenient to participants. The nutritional intervention is planned for the late-spring/early-summer months since, in general, women are more motivated to lose weight before the summer [45].

**The inclusion criteria are** women, age 18–45; overweight or obesity type I (BMI 25.5–35); motivated to lose weight and motivated and willing to participate in a nutritional intervention trial.

**The exclusion criteria are** pregnancy, childbearing age not using contraceptives, breastfeeding, type 1 or type 2 diabetes, any chronic diseases requiring pharmacotherapy; participation in other clinical trials; severe obesity (BMI > 35), and any diagnosed psychiatric disorders.

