### Sample size

On trial opening, the first 80 women meeting eligibility criteria who also do not meet any of the exclusion criteria will be selected. The focus on only female subjects was based on eliminating biological sex as a factor that could affect the results. Moreover, it is scientifically proven that women have better trust in healthy nutrition and more engagement and compliance in dietary programs [46, 47], thus a lower number of drop-outs is expected. At the end of the intervention, dietary efficacy is projected to be between the equivalent of one dress size to one and a half dress sizes, equating to a weight loss of approximately 5kg. For BMI between 28 and 35, the standard deviation of weight is approximately 5kg equating to an intra-group standardised effect of 1. However, a downward revision in standardised effect size for a between groups comparions for an intent-to-treat analysis Analysis of Covariance (ANCOVA) would indicate that n = 32 women per group would have at least 80% power to detect a standardised difference of Cohen’s d = 0.5 (alpha = 0.05, two-sided) assuming a pre- post- correlation in weight of 0.7. Inflation of sample sizes to account for loss to follow-up would indicate n = 40 per group would provide a safety margin for a comparison between group means. This sample size is conservatively consistent with Mohorko et al. [39]. The sample size will support within-groups, between-groups, and whole-group analyses for the secondary research questions.

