### Randomization and blinding

The study participants will be randomly divided into two experimental groups. Stratified randomisation will be performed based on age and BMI. The KD group will receive a 1700 kcal ketogenic diet (fat: protein: carbohydrate ratio of 70:20:10), while the control group will receive a 1700 kcal standard balanced diet (fat: protein: carbohydrate ratio 20:30:50). Both participants and the researchers will not be blinded due to character of the intervention.

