### Statistical analysis plan

The data from this two-arm parallel randomised controlled trial is amenable to analysis using standard statistical techniques. These analyses will be undertaken using STATISTICA v. 13.3 (StatSoft, Tulsa, USA) and IBM SPSS version 28.

The primary analysis for each outcome will be by intention-to-treat, meaning that all eligible consenting participants on whom an outcome is available will be included in the analysis. All statistical tests will be two-sided. A nominal significance level of alpha = 0.05 will be used to judge significance. Where appropriate, statistical significance after controlling for the False Discovery Rate will be additionally undertaken using the Benjamini-Hochberg procedure.

For each analysis, the following summaries will be provided:

The number of participants who are included in the analysisA relevant summary measure of the outcome after an appropriate transformation (e.g., mean (SD), median (IQR) or number (%))Statistical analyses will report the effect size, 95% confidence interval and a p-value. P-values will be reported to three decimal places except where p < .001.

Analyses will be supplemented with appropriate graphical displays.

The primary outcome, weight at T2, will be compared between groups using analysis of covariance controlling for weight at T0. In general, parametric tests will be used with scale outcome data. If, for any particular analysis, there are doubts to the assuredness of validity of a parametric test then an analogous non-parametric test, will be used. ANCOVA and the non-paramteric Quade test will be used to compare randomised arms after controlling for commensurate baseline data. Simple differences between groups will be analysed using the independent sample t-test or the nonparametric Mann-Whitney test. Chemometric analyses will additionally use Principal Components Analysis (PCA), Partial Least Squares regression (PLSR) and Mutlivariable Discriminant Analysis (MDA) will be performed. The results of volatile organic compounds will be analysed using the XCMS-online platform for metabolomics. All the obtained results will be numerical and conducted in triplicates or duplicates, as appropriate.

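### The between-arm ANCOVAs leave out the stratification factors age and BMI; adding them costs almost nothing and would probably gain a little precision

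*Protocol article*

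**What the plan says.** The Randomization and blinding section of the protocol article fixes the allocation method: "Stratified randomisation will be performed based on age and BMI". Cut-points, number of strata and block size are not given there, which is usual for an article.

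The Statistical analysis plan section fixes the primary model: "The primary outcome, weight at T2, will be compared between groups using analysis of covariance controlling for weight at T0". For between-arm comparisons in general, it says that ANCOVA and Quade's test "will be used to compare randomised arms after controlling for commensurate baseline data". No section brings age, BMI or the strata into a between-arm model.

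The Sample size section rests on an ANCOVA with "d = 0.5 (alpha = 0.05, two-sided) assuming a pre- post- correlation in weight of 0.7" and concludes that this "would indicate that n = 32 women per group would have at least 80% power".

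**The concern.** Stratified randomisation balances the arms on age and BMI, so these factors contribute little to the chance difference between arms. A model without them still leaves whatever outcome variation they explain in the residual. The model-based standard error then overstates the true sampling variability of the treatment estimate. Confidence intervals are wider than they need be, and the test runs below its nominal 5% level.

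The usual remedy is to carry the stratification factors into the analysis. With 32 to 40 women per arm, even a modest gain in precision is worth having when it is free. Adjustment also deals with imbalance on the factors that arises when women drop out.

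All of this depends on one condition: age and BMI must predict the outcome after the baseline value is in the model.

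**Working it through.** **Inputs from the Sample size section.** Two-sided alpha 0.05, d = 0.5, pre-post correlation r = 0.7, SD of weight about 5 kg, 32 per group, 40 per group after inflation. **Assumed, because the article gives no figure:** the partial R-squared of age and BMI for T2 weight given T0 weight, taken as 0 to 20%.

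**Step 1: reproduce the plan's figure.** For ANCOVA on T0 weight alone,

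n = 2(1 - r²)(z₀.₉₇₅ + z₀.₈₀)² / d² = 2 × 0.51 × (1.960 + 0.842)² / 0.25 = 32.02 per group.

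This agrees with the stated 32. Without adjustment the formula gives 63, and for a change score 38, so the T0-only ANCOVA is clearly the basis. Power at 32 is 79.97% by the normal approximation and 78.7% by the noncentral t. Inflation for 20% loss gives 32 / 0.8 = 40.

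**Step 2: add age and BMI.** The residual SD is multiplied by √(1 - partial R²), and two more degrees of freedom are spent. Power comes from the noncentral t with noncentrality d / (σ√(2/n)), where σ = √0.51 × √(1 - partial R²). In kilograms, the T0-only standard error at 32 per group is 5 × √0.51 × √(2/32) = 0.893 kg.

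| Partial R² | SE ratio | SE, kg | Power, 32 per group | Power, 40 per group |
|---|---|---|---|---|
| 0 | 1.000 | 0.893 | 78.7% | 87.1% |
| 5% | 0.975 | 0.870 | 80.7% | 88.7% |
| 10% | 0.949 | 0.847 | 82.7% | 90.3% |
| 20% | 0.894 | 0.799 | 86.9% | 93.3% |

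**Step 3: check by simulation that omission is conservative.** Settings: 64 women, 2 × 2 strata, permuted blocks of 4, no loss; 6,000 runs under the null and 3,000 under d = 0.5.

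| Partial R² (about) | Mean SE, T0 only | Mean SE, T0 + strata | Type I error, T0 only | Power, T0 only | Power, T0 + strata |
|---|---|---|---|---|---|
| 0 | 0.179 | 0.180 | 4.9% | 77.4% | 77.0% |
| 3% | 0.181 | 0.179 | 4.9% | 77.3% | 78.2% |
| 11% | 0.190 | 0.179 | 4.3% | 74.4% | 78.2% |
| 28% | 0.212 | 0.180 | 2.9% | 66.0% | 78.6% |

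The Monte Carlo error is √(0.05 × 0.95 / 6000) = 0.3 points on type I error and about 0.7 points on power. The 4.9% therefore cannot be told from 5%, while the 2.9% clearly can. With strata in the model, type I error was 5.1 to 5.2% throughout.

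The falling T0-only power in this table follows from how it was set up: the residual variance after the strata was held at 0.51, so the T0-only residual grows with the strata effect. The plan's r = 0.7 instead fixes the T0-only residual, as in Step 2.

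**Step 4: the cost if the factors explain nothing.** The mean standard error rises from 0.1788 to 0.1795, or 0.4%. With 80 randomised and 20% lost at random, the rise is about 0.6%.

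**Step 5: which part of the range is plausible for weight.** The residual SD after T0 weight is 5 × √0.51 = 3.57 kg, a variance of 12.75 kg². A two-level factor that splits the women in half and shifts the mean by b contributes b²/4. For two equal, independent factors to explain 20%, 2 × b²/4 = 0.20 × 12.75, so b = 2.3 kg each between women of the same T0 weight. For 5%, b = 1.1 kg. The projected weight loss is about 5 kg, so 20% would need large effects.

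**The case against.** The strongest reply is that nothing stated in the article is wrong. The trial was sized for the model that it plans to fit, with no credit taken for stratification. Leaving the factors out makes the test conservative at worst.

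BMI is weight over height squared, so T0 weight already carries much of the BMI stratum. What remains is mainly height, plus age between 18 and 45. The gain for the primary outcome may be nil. The article also condenses a fuller plan that may name these covariates, and its wording does not exclude others.

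Most of this stands and limits the point to an improvement. It does not remove it. The analysis section names the outcome, time point, method and covariate, so this is a stated model, and a fuller plan that adds the factors should agree with it. Some residual association is also plausible, although the article offers no figure. Every woman receives 1700 kcal whatever her size or age, so the energy deficit may vary with height and age. In the secondary ANCOVAs, T0 weight is not a covariate and cannot stand in for BMI. No calculation was made for those outcomes.

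A reader might infer that the standard error is certainly too wide, or that the trial falls short of its planned power. The documents support neither. The first depends on an association that they do not quantify, and the second is contradicted by Step 1.

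**Conclusion.** The mismatch between stratified randomisation and the stated covariates is real, and the direction of its effect is clear. Its size is conditional and, for weight, probably small. At a partial R-squared of 0 to 5%, adjustment reduces the standard error by 0 to 2.5% and adds at most about 2 points of power at 32 per group. The gain becomes material only from about 10% upwards (about 5% in standard error and 4 points of power).

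These figures assume r = 0.7 for the T0-only model, additive effects of the factors and, in the simulation, a 2 × 2 stratification that the article does not specify. The treatment estimate is not biased, type I error is not inflated, and the planned sample size stands. This is a nearly free improvement to the plan, not an error in it.

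**What to change.** State the primary model as: weight at T2 = arm + weight at T0 + age + BMI at T0. Age and BMI can enter in the form used for randomisation or as continuous T0 values; the plan should say which. Include the same two factors, with the baseline value of the outcome, in the secondary between-arm ANCOVAs.

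Fix the wording before outcome data are examined. The trial is open-label, and covariates added later could look data-driven.

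The cost is a line of text and about two degrees of freedom (more if a factor has more than two levels). The standard error would be about 0.6% wider if the factors explain nothing. No new data are needed, since age and BMI are known at T0, and the sample size need not change.

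### An undefined doubt can replace the primary ANCOVA with a rank test that does not itself give the adjusted difference in kg, in an unblinded trial

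*Protocol article*

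**What the plan says.** The section Statistical analysis plan names one primary test: ANCOVA on T2 weight with T0 weight as covariate. Parametric tests are the default for scale outcomes. The section then adds a switch that covers every analysis: if "there are doubts to the assuredness of validity of a parametric test then an analogous non-parametric test, will be used".

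The section names two pairs of tests. ANCOVA and the Quade test compare the randomised arms with control for the matching baseline value. The second pair has a different role: "Simple differences between groups will be analysed using the independent sample t-test or the nonparametric Mann-Whitney test". What counts as a simple difference is not defined.

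For each analysis the plan "will report the effect size, 95% confidence interval and a p-value". On error control it states: "A nominal significance level of alpha = 0.05 will be used to judge significance", and "All statistical tests will be two-sided".

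The section Sample size rests on ANCOVA: "n = 32 women per group would have at least 80% power to detect a standardised difference of Cohen’s d = 0.5", "assuming a pre- post- correlation in weight of 0.7". The section Randomization and blinding says that neither participants nor researchers are blinded.

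**The concern.** The primary test is named, but the switch rule then makes that choice conditional. The rule gives no diagnostic, threshold, timing or decision-maker, and it does not exempt the primary analysis. The people who hold the doubt may know who is in which arm.

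Three things are at stake:

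- **Error control.** The primary p-value is not fully fixed in advance. Choosing between two valid tests with the result in view pushes type I error above 5%.
- **The quantity reported.** The trial is planned around kg lost. The Quade test works on residuals of ranks and does not itself return a baseline-adjusted difference in kg.
- **Power and precision.** The sample size belongs to ANCOVA, and the fallback is weaker on normal data. Separately, the undefined second category leaves room for unadjusted tests on outcomes that have a T0 value.

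**Working it through.** **Inputs from the protocol article.** Two-sided alpha 0.05 (Statistical analysis plan); d = 0.5, r = 0.7 for weight, 32 per arm before and 40 per arm after inflation (Sample size).

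**Step 1: reproduce the plan's figure.** ANCOVA multiplies the outcome variance by 1 − r² = 1 − 0.49 = 0.51, so the residual SD is √0.51 = 0.714 in SD units.

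- n per arm = 2 × (1.960 + 0.842)² × 0.51 / 0.5² ≈ 32.0, which rounds up to 33.
- Power at 32 per arm is 0.7997 by the normal approximation and 0.787 by the noncentral t with 2n − 3 degrees of freedom.
- 32 / (1 − 0.20) = 40. The 20% loss is implied, not stated.

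The plan's figure is reproduced, and it belongs to ANCOVA.

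**Step 2: what the switch does to error and power.** Simulation with 20,000 runs per setting and r = 0.7, using bivariate normal data or the same data exponentiated (lognormal). Quade: rank T0 and T2 over both arms, regress the T2 ranks on the T0 ranks, and compare the residuals between arms. The fixed check uses Quade if Shapiro-Wilk on the ANCOVA residuals gives p < 0.05, and ANCOVA otherwise.

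| Rejection rate | ANCOVA | Quade | Smaller p of the two | Fixed check |
|---|---|---|---|---|
| Null, normal, 32 per arm | 4.8% | 4.8% | 6.2% | 4.9% |
| Null, normal, 40 per arm | 5.2% | 5.0% | 6.6% | 5.2% |
| Null, lognormal, 32 per arm | 4.1% | 4.8% | 7.4% | 4.8% |
| d = 0.5, normal, 32 per arm | 77.7% | 73.3% | not a valid 5% test | 77.5% |
| d = 0.5, lognormal, 32 per arm | 52.4% | 73.3% | not a valid 5% test | 73.3% |

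The Monte Carlo standard error near 5% is √(0.05 × 0.95 / 20,000) = 0.15 points. Repeat runs on normal data at 32 per arm gave about 6–7% for the smaller p, 77–79% power for ANCOVA and 72–73% for Quade.

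In the last row, d applies on the log scale. Taking logs returns the normal data exactly, so ANCOVA on the log scale has the 77.7% of the row above, more than Quade.

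**Step 3: the quantity reported.** Sample size puts the SD of weight at about 5 kg, so d = 0.5 is 0.5 × 5 = 2.5 kg. ANCOVA estimates that adjusted difference with its interval. The Quade test gives a p-value for rank residuals; a kg estimate would have to come from another analysis, which the plan does not name.

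**Step 4: which outcomes have a T0 value.** Weight, body composition, circumferences and blood pressure (Sample collection), every listed blood and breath assay, urine, the food frequency questionnaire and quality of life are all measured at T0. Diary side effects and diet compliance are not.

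**Step 5: cost of ignoring T0.** Relative to ANCOVA, an unadjusted test faces a variance larger by 1 / (1 − r²):

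- r = 0.7 (stated, for weight only): 1 / 0.51 = 1.96, so 63 per arm instead of 33. At 32 per arm, power is 50–52% instead of 79–80%.
- r = 0.5 (assumed): 1 / 0.75 = 1.33.
- r = 0.3 (assumed): 1 / 0.91 = 1.10.

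**The case against.** The strongest reply is that the plan names its primary test and ties the switch to the validity of a test, not to its result. The fixed-check column supports this: a switch driven only by an assumption check stays near 5%. The 6–7% is what always taking the smaller p-value would produce, and nothing in the text says that this will happen. This stands, and it limits the size of the point.

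Second, this is a condensed article, and a separate analysis plan may define the criterion. That would excuse silence. But the article is not silent: it states a rule under which the primary test is replaced on an undefined judgement.

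Third, using Quade for the p-value does not forbid reporting a mean difference beside it. True, but that estimate and interval would come from a different analysis than the test, and the plan does not say which.

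Fourth, with strongly skewed data the rank test beats raw-scale ANCOVA (73.3% against 52.4%). That is a good argument for a transformation named in advance. It does not support an open switch.

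A reader might infer more than the documents support:

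- *That four tests are interchangeable for one comparison.* The switch moves only from a test to its analogue. The adjusted pair is assigned to randomised arms with a matching baseline.
- *That the switch will be made after the data are seen.* The text gives no timing.
- *That secondary outcomes will be tested without T0 and lose much of their power.* The plan does not say so, and no correlation is given for them.

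**Conclusion.** The point holds in a limited form. ANCOVA is fixed for T2 weight, but an undefined doubt may replace it with the Quade test in an unblinded trial. If the result steered that choice, type I error could reach about 6–7% at 32 per arm (normal data, r = 0.7); with a fixed check it stays near 5%. The plan's wording permits this inflation but does not make it happen.

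Two consequences do not depend on anyone steering the choice. The fallback does not itself deliver the adjusted kg difference and 95% interval that the plan promises. On normal data it also has about 72–73% power, against 77–79% for the test behind the sample size.

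The undefined category of simple differences is a smaller wording gap. Its cost depends on the pre–post correlation, which is stated for weight only. The figures rest on equal arms, the stated d and r, and normal or lognormal data.

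**What to change.** 1. **Weight.** Keep baseline-adjusted ANCOVA as the primary test whatever the shape of the residuals. Allow a robust-variance or bootstrap 95% confidence interval as the only fallback. Show the Quade test as a sensitivity analysis only.
2. **Skewed assays.** Name in advance which assays will be analysed by ANCOVA on the log scale, with T0 as covariate, and report ratios of geometric means with 95% intervals.
3. **Unadjusted tests.** State that the t-test and Mann-Whitney test apply only to variables without a T0 value, such as diary side effects and diet compliance.

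This keeps the estimate in kg and the test that was powered. The cost is a few sentences in the plan and slightly more analysis work; there is no extra data collection and no change in sample size.

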### Data management plan

To protect the participants’ privacy and to maintain confidentiality, all personal data will be stored in password-protected files and secured against unauthorized access by third parties. The raw data and materials are only accessible to project team members. Each participant will be assigned a randomly generated code that does not allow any conclusions to be drawn about the person. Only this code will be used for naming files and samples. Only completely anonymized data will be made available to other researchers after the completion of the study or in data repositories. Only mean values and group statistics will be reported in publications.

## Discussion

We designed this prospective, single-centre, randomised controlled study to evaluate the efficacy and the effect of KD on health-related parameters in women with overweight and obesity. Obesity is a common, serious, and costly chronic disease of adults and children, which requires intervention to reduce the risk of the development of chronic diseases.

The KD is a dietetic regime with a limited intake of carbohydrates, which consists mainly of the consumption of fat which leads to a ketosis state in the body. Although originally, KD was designed for the treatment of epilepsy [56], there has been over the past few years, a societal increasing trend in following KD for body weight reduction. There is some evidence that a KD can result in a better dynamic of body weight loss at the beginning of the intervention [19]. In general, the results of studies with very low-calorie KD have reported KD to have benefit in losing weight and decreasing BMI and can confer positive effects on the human body [28, 57]. However, there is a lack of studies with a calorie-controlled control group. To investigate this knowledge gap we have described a study protocol of a comprehensive experiment that investigates the effects of KD as a weight management diet in women with overweight and obesity, with particular emphasis on inflammation, oxidative stress, nutritional status and metabolism.

